# Improving Blood Pressure Among African Americans With Hypertension Using a Mobile Health Approach (the MI-BP App): Protocol for a Randomized Controlled Trial

**DOI:** 10.2196/12601

**Published:** 2019-01-25

**Keywords:** hypertension, mHealth, blood pressure, smartphone, mobile phone

## Abstract

**Background:**

African Americans shoulder significant disparities related to hypertension (HTN), which is a serious public health problem in the city of Detroit, Michigan, where more than 80% of the population is African American. Connectivity through smartphones, use of home blood pressure (BP) monitoring, and newly developed mobile health (mHealth) interventions can facilitate behavioral changes and may improve long-term self-care for chronic conditions, but implementation of a combined approach utilizing these methods has not been tested among African American patients with uncontrolled HTN. Since African Americans are more likely than other racial or ethnic subgroups to utilize the emergency department (ED) for ambulatory care, this presents an opportunity to intervene on a population that is otherwise difficult to reach.

**Objective:**

The MI-BP app aims to reduce health disparities related to HTN in the community by employing a user-centered intervention focused on self-BP monitoring, physical activity, reduced sodium intake, and medication adherence. We seek to test the efficacy of MI-BP, an mHealth app for HTN self-management, on BP control (primary aim), physical activity, sodium intake, and medication adherence (secondary aim) in African Americans with HTN. This study also seeks to evaluate the cost-effectiveness of MI-BP when compared with usual care methods.

**Methods:**

This is a 1-year randomized controlled trial that will recruit individuals who have uncontrolled HTN from 2 EDs in the city of Detroit, with a planned sample size of 396 randomized participants. To be eligible for inclusion, potential participants must be African American, 25 to 70 years old, previously diagnosed with HTN, have a smartphone compatible with MI-BP, and have uncontrolled BP at triage and on repeat measurement at least 1-hour post triage vitals. Once a participant is deemed eligible, all study procedures and subsequent follow-up visits (8 in total) are conducted at the Wayne State University Clinical Research Service Center. We seek to determine the effect of MI-BP on BP for 1 year (using BP control and mean systolic BP as coprimary outcomes and physical activity, sodium intake, and medication adherence as secondary outcomes) compared with usual care controls.

**Results:**

Recruitment for this study began in January 2018. The study will continue through 2021.

**Conclusions:**

As the first of its kind conducted in an ED setting, MI-BP was designed to document the efficacy and acceptability of a multicomponent mHealth approach to help African Americans with uncontrolled BP modify their lifestyle to better manage their HTN. We expect to lay the foundation to sustainably reduce HTN-related health disparities through better integration of multiple behavior self-monitoring and improve outcomes for those who traditionally rely on the ED for chronic disease care.

**Trial Registration:**

ClinicalTrials.gov NCT02360293; http://clinicaltrials.gov/ct2/show/NCT02360293

**International Registered Report Identifier (IRRID):**

RR1-10.2196/12601

## Introduction

### Background

Hypertension (HTN) is one of the most important cardiovascular disease risk factors affecting more than 100 million Americans under the new American College of Cardiology/American Heart Association (AHA) guidelines [1,2]. However, only about half of those with HTN achieve blood pressure (BP) control, and about 15.9% remain unaware of their condition [3]. Compared with whites, African Americans are more likely to develop HTN and have uncontrolled BP [4], increasing the risk of premature cardiovascular morbidity and mortality. African Americans are also more likely to utilize the emergency department (ED) for ambulatory care of chronic conditions such as HTN [5], a factor strongly linked with adverse cardiovascular events and diminished awareness of HTN [6], as well as lower BP control [7]. Although there are many reasons for such patterns of ED utilization, including poor access to primary care, and the ability to receive care at all hours regardless of the ability to pay, it serves to highlight the challenges certain populations face, which may have downstream effects on self-management.

Recommendations for improving HTN-related outcomes have been consistent for decades: maintain a healthy weight, reduce daily sodium intake, increase physical activity, and comply with antihypertensive therapy, as prescribed [8]. Despite strong evidence supporting these recommendations, facilitating the necessary behavior changes in patients with HTN remains difficult. African Americans, in particular, are less likely than whites to report adherence with such lifestyle and behavioral changes [3]. Moreover, existing interventions for improving BP typically focus on targeting 1 behavior, which may not be sufficient for improving BP control [9-12]. However, comprehensive evaluations of multiple health behavior change interventions, especially as they relate to BP control among African Americans, are lacking from the literature.

Accordingly, we sought to develop and test a mobile health (mHealth) approach to deliver a multiple behavior change intervention targeting BP reduction in African American ED patients with uncontrolled HTN. About 95% of American adults own some form of a mobile phone, and smartphone adoption is about the same in white and African American populations (77% and 75%, respectively) [13], yet African Americans are more dependent on smartphones for internet access than whites (24% vs 14%, respectively) [14], suggesting that an mHealth approach may be particularly useful in this population. Since BP is routinely measured in EDs, visits to the ED provide a unique opportunity to both identify patients with uncontrolled HTN and intercede, particularly in African American communities where regular interaction with the health care system may be lacking.

### Study Objective

The purpose of this study is to establish the efficacy of MI-BP, a multiple behavior change intervention delivered via mHealth that supports achieving and maintaining BP control in African Americans who have uncontrolled HTN and are recruited from 2 urban EDs. This study also seeks to evaluate the cost-effectiveness of MI-BP compared with enhanced usual care methods.

Our primary study aim is to determine the effect of MI-BP on BP for 1 year (using BP control and mean systolic blood pressure [SBP] as coprimary outcomes) compared with usual care controls, in a 1-year randomized controlled trial (RCT) (NCT02955537). We hypothesize that at 1 year, BP control rates will be significantly greater in the MI-BP arm than in usual care. We also hypothesize that at 1 year, mean SBP will be significantly lower in the MI-BP arm than in usual care. Our second aim is to determine the effect of MI-BP on secondary outcomes (physical activity, sodium intake, and medication adherence) compared with usual care controls, in a 1-year RCT. We hypothesize that at 1 year, measures of physical activity, sodium intake, and medication adherence will be significantly better in the MI-BP arm than in usual care. Our third aim is to evaluate the cost-effectiveness of MI-BP compared with usual care methods. We hypothesize that the MI-BP approach will provide good value for money, both within-trial and long term. Here we describe the MI-BP approach that was developed for this study.

## Methods

### Overview

This is a 1-year, 2-arm, RCT of MI-BP versus enhanced usual care plus follow-up. The methods for this study have been approved by Wayne State University’s (WSU) Institutional Review Board (IRB#: 040416M1F) and the University of Michigan IRBMED (HUM00114202).

### MI-BP Intervention Description

MI-BP is a comprehensive, user-centered, multicomponent intervention that targets multiple behavior changes for managing HTN. The MI-BP intervention was developed building on our previous work with the BPMED text message intervention to improve HTN medication adherence in the same population [15]. Our design process incorporated target end user feedback from the Hypertension Community Advisory Board in Detroit, Michigan.

The MI-BP intervention includes a smartphone-based app that incorporates the following components, which users are encouraged but not required to use. Vibrent Health (Fairfax, VA), a digital health company, was engaged to develop the app, online portal, and server platforms necessary to support this project.

#### Home Blood Pressure Monitoring and Tracking

MI-BP allows users to revicew both 1- and 4-week graphs of BP readings, collected via study-issued home BP cuffs. In addition to graphs, numerical logs of 1- and 4-week BP data are also available for review (see Figure 1 for screenshots of the MI-BP app). BP data can be either digitally synced, or manually entered into the MI-BP app. Participants with arm circumferences of 23 to 45 cm, which represents the majority of users, will receive a Bluetooth-enabled digital BP monitor (A&D UA-651BLE) that can store up to 30 BP measurements. With a touch of a button, this cuff can automatically sync collected measurements with the MI-BP app. For the participants who have an arm circumference between 42 and 60 cm, we will provide an extra-large arm monitor (LifeSource A&D UA-789). These cuffs are not Bluetooth-enabled and require manual data entry.

Users are instructed to measure and sync (or manually enter) their BP to the MI-BP app, at home, for a minimum of at least 3 days per week; however, daily self-monitoring and syncing are encouraged. When taking BP at home, users are instructed to take 3 consecutive readings and adhere to the following guidelines:

Relieve yourself in the bathroom before taking BP, if needed.Keep arm at heart level by resting it on a table during monitoring.Sit in a chair with a back and with feet flat on the floor for at least 5 min before taking BP.Avoid tobacco, caffeine, or alcohol for 30 min before taking BP.Avoid taking BP right after exercise, when emotionally upset, or in pain.Avoid talking while taking BP.

In the event that a participant records a BP with systolic reading of greater than 180 mmHg or less than 100 mmHg, or a diastolic reading of greater than 110 mmHg, the MI-BP users are then instructed by the study staff at baseline, as well as by automated notifications within the app at the time of the elevated reading, to do the following:

Wait for 5 min and then check BP again.If the SBP is still above 180 mmHg or less than 100 mmHg, or if the diastolic BP is still above 110 mmHg for 3 days in a row, call the research staff.Report to the ED and follow up after with a call to the research staff if experiencing symptoms of dizziness, chest pain, severe headache, visual changes, or numbness or weakness in face or extremities.

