Randomization is stratified by sex in blocks of equal size, allowing us to investigate sex as an effect-modifying biological variable. To control response fatigue, we created 6 different permutations of the baseline survey, each with a different order of instruments, which are also balanced within blocks. The research assistants responsible for arm allocation are blinded to block size to prevent contamination.

After randomization, all study materials, including any equipment and/or materials, are distributed to the participants according to the treatment arm. Medication titration occurs again at week 8, and at subsequent follow-up visits at weeks 13, 26, 39, and 52 to ensure optimal treatment. Data collection follow-up visits take place at weeks 13, 26, 39, and 52, where a consistent set of study measures is collected—BP, health status, weight, adherence to BP measurements, physical activity, sodium intake, and medication adherence self-monitoring. Technology acceptance measures, including perceived ease of use and perceived usefulness, are also collected.

For medication titration and follow-up visits, patients are instructed to bring their HTN medications with them so pill counts can be conducted. Pill counts are used to avoid prescribing potentially harmful up-titration in antihypertensive therapy for patients with elevated BP at follow-up visits that may be because of medication noncompliance. For patients who self-report not filling prescriptions between visits, or when the expected number of pills found in the participant’s medication bottles (based on dosage and dispense date) suggests a less than 80% medication adherence, we continue with the same regimen without adjustment. We also monitor for any potentially harmful renal or metabolic issues at weeks 0, 26, and 52 and adjust medications accordingly. In addition to the medications, participants are instructed to bring study-dispensed devices so data can be downloaded, and adherence to self-monitoring behaviors can be ascertained.

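### A user who measures home BP on the stated minimum of 3 days a week may never meet the three-day condition for calling staff about a diastolic reading above 110 mmHg

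*Protocol article*

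**What the plan says.** All the relevant instructions stand in one section of the Protocol article, Home Blood Pressure Monitoring and Tracking.

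- **Measuring schedule.** Users measure and sync or enter their BP "for a minimum of at least 3 days per week; however, daily self-monitoring and syncing are encouraged". Nothing asks for the days to be consecutive. The MI-BP Intervention Description adds that the app contains components "which users are encouraged but not required to use".
- **What starts the instruction.** A "systolic reading of greater than 180 mmHg or less than 100 mmHg, or a diastolic reading of greater than 110 mmHg".
- **How the user learns of it.** From study staff at baseline, "as well as by automated notifications within the app at the time of the elevated reading".
- **What the user then does.** Recheck after 5 minutes. Call the research staff if the systolic value is still outside its limits, "or if the diastolic BP is still above 110 mmHg for 3 days in a row, call the research staff". A separate line sends users with listed symptoms to the ED, followed by a call to staff; it has no three-day condition.

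On scheduled contact, Procedures states: "Medication titration occurs again at week 8, and at subsequent follow-up visits at weeks 13, 26, 39, and 52".

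**The concern.** A persistence condition can work only if the measuring schedule can produce the readings it needs. Here the schedule allows gaps between measuring days, the diastolic condition is worded as an unbroken run of days, and nothing in the article asks for readings on the days after an out-of-range value. A participant can therefore do everything asked and still be unable to satisfy the rule, however persistent the finding.

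The sentence has a second weakness. It joins a systolic clause and a diastolic clause and puts the three-day wording at the end. A participant, or a staff member explaining it, can take that wording to cover the diastolic limit alone or both clauses.

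At stake is a safety instruction that the protocol itself thought necessary, in a population enrolled because its BP is uncontrolled. If the condition is not met and the user does not call for another reason, the next scheduled BP check is the next clinic visit.

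**Working it through.** The plan gives no figure to reproduce on this point. The check is whether the schedule can satisfy the rule.

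**Inputs.** Minimum of 3 measuring days a week, days not specified; a diastolic condition of three days in a row; a 5-minute recheck as the only stated follow-up measurement (all from Home Blood Pressure Monitoring and Tracking). Titration and data collection visits at weeks 2, 8, 13, 26, 39 and 52 (Table 1 and Procedures).

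**Assumptions for the count.** The days in a row are calendar days. The user keeps the same weekdays every week, and a run may cross the weekend. Every diastolic reading is out of range and the user has no symptoms.

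**Step 1: 3 days a week.** There are C(7,3) = 35 weekday patterns. A pattern contains three consecutive days only if it is one of the 7 blocks that start on a given weekday. So 35 − 7 = 28 patterns (28/35 = 80%) never meet the condition.

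**Step 2: more than 3 days a week.** With 4 measuring days, the 3 days off split the week into 3 gaps that hold 4 measuring days in total. No run of three means that no gap holds more than 2. The ordered splits are three arrangements of (2,2,0) and three of (2,1,1), 6 in all, which gives 7 × 6 / 3 = 14 patterns. With 5 measuring days there are only 2 gaps, which hold at most 2 + 2 = 4 days without a run, so a run of three is unavoidable. A full enumeration agrees:

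| Days per week | Patterns | No run of three | Share |
|---|---|---|---|
| 3 | 35 | 28 | 80% |
| 4 | 35 | 14 | 40% |
| 5 | 21 | 0 | 0% |
| 6 | 7 | 0 | 0% |
| 7 | 1 | 0 | 0% |

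If runs are counted only within one Monday-to-Sunday week, 30 of 35 three-day patterns (86%) contain no run.

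**Step 3: the other meaning of the count.** If successive measuring days are meant, the Monday/Wednesday/Friday user meets the condition on Friday. For any fixed 3-day pattern, three successive measuring days fall within 7 calendar days, so no pattern fails.

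**Step 4: the scope of the condition.**

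| Three-day wording governs | Calendar days | Measuring days |
|---|---|---|
| Diastolic limit only (literal) | Diastolic condition may never be met; systolic value still out of range at recheck means a call that day | No gap |
| Both clauses | Either condition may never be met | No gap |

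The diastolic gap is therefore present under either scope whenever calendar days are meant.

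**Step 5: time to the next visit.** Week 2 to 8 is 6 weeks, week 8 to 13 is 5 weeks, and the later intervals are 13 weeks each, or 13 × 7 = 91 days. These are the longest possible waits, not typical ones.

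**The case against.** The strongest reply is that the three-day figure is a routine floor. Daily measurement is encouraged in the same sentence, and a user who has just been notified that three days matter may well measure on the next two. The actual notification text is not shown; the article only summarises it. The count of patterns also needs calendar days, and the gap vanishes if measuring days are meant. All of this is fair. It shows that the rule can work in practice, but not that the stated minimum makes it work.

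There are other routes to help. Symptomatic users go to the ED. Procedures says that participants may call staff with questions about their BP, and the intervention arm has in-app messaging. It would therefore be wrong to infer that the rule is the only contact between visits. These are, however, a symptom route and a general invitation. Neither is a trigger for an asymptomatic out-of-range reading.

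A reader might also draw stronger conclusions that the document does not support:

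- *Users are never told to call.* They are told the rule at baseline and by notification. What may never occur is the condition.
- *The failure covers every out-of-range reading.* Read literally, the systolic clause stands alone and leads to a call after the recheck.
- *It affects most users.* The article does not say which days users measure.
- *The two recruiting sites would instruct participants differently.* Clinical Setting puts all visits after enrolment at one centre.
- *Nobody on the study side looks at the readings.* A condensed article commonly leaves such handling to the full protocol, so its silence is no finding.

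**Conclusion.** The concern stands in a limited form. The measuring instruction and the diastolic call condition do not fit together on the plain calendar-day reading: a symptom-free user who does exactly what is asked may never meet the condition. The size is 28 of 35 fixed weekly patterns at the stated minimum, 14 of 35 at 4 days a week, and none from 5 days upward. This weights all patterns equally and supposes that no extra measuring days follow an out-of-range reading; it is not an estimate of how many participants are affected. Whether the gap extends to the systolic limits depends on a sentence that the article leaves open. No sample size or primary analysis figure depends on it. It is still worth correcting before further participants are instructed, because it concerns a safety rule that can fail when followed to the letter.

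**What to change.** Reconcile the minimum measuring schedule with the persistence condition, in both the participant instructions and the app notification, so that a participant who measures as instructed can meet the condition. In the same wording, state which limits the condition governs (systolic, diastolic or both) and what *in a row* counts (calendar days or measuring days). The study physicians and the Data Safety Monitoring Board should decide the clinical content; this review proposes no limit, count or schedule.

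The cost is a revised instruction sentence and matching notification text, and possibly some additional calls for staff to take. It needs no new visits or participants.

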#### Physical Activity Monitoring and Tracking

MI-BP also allows users to view numerical logs, as well as 1- and 4-week graphs of physical activity data, such as steps counts and miles collected via study-issued Fitbit Zip pedometers (see Figure 1 for screenshots of the MI-BP app). These devices can store up to 30 days of step-count data. Recent work by Tully et al found the Fitbit Zip to be a valid measure of physical activity in free-living adults [16]. Users are instructed to wear their Fitbit daily and to sync the device at least once per week.

#### Sodium Intake Monitoring and Tracking

In addition to BP and physical activity, MI-BP allows users to track their daily intake of high-sodium foods using a checklist approach and monitor their intake over time with 1- and 4-week graphs. Rather than asking users to self-report all of the food they eat in a day, we take a more adaptive approach to estimate sodium intake. The MI-BP users are asked to self-monitor their intake of high-sodium foods, using a checklist-type log available within MI-BP. Our checklist comprises 7 categories, with 3 to 8 items per category. The categories and items included within were based on resources from the University of California, San Francisco [17], Centers for Disease Control and Prevention [18], and work by Smith et al [19], and they were refined based on our own team’s expertise working within this target population. Each time an MI-BP user eats one of the foods on the checklist (regardless of portion size), we ask the participants to indicate this within the sodium log. At the end of the day, users should have a count of the number of times a high-sodium food was consumed in the day. Although we encourage users to track their intake of high-sodium foods daily, this is not required (see Figure 1 for screenshots of the MI-BP app).

#### Goal Setting

Physical activity goal setting is conducted weekly and step-count goals are displayed within the MI-BP app, as well as sent to users via push notification. Step-count goals are gradually incremented based on previous work from our team [20-24] and are calculated based on an average of 7 consecutive days of data, during which at least 5 of the days must be valid (ie, more than 200 steps per day). Calculated goals are never more than 600 steps more than the previous goal, which allows goals to be gradually incremented in order to reduce adverse events.

**Figure 1 figure1:**
[figure not shown]
Screenshots from the MI-BP app.

Sodium intake goal setting is conducted every 2 to 4 weeks, and sodium intake goals are displayed within the MI-BP app, as well as sent to users via push notification (see Figure 1 for screenshots of the MI-BP app). MI-BP users are instructed to intensively self-monitor their diet every day for the first week of their intervention period. This 1-week period serves 2 purposes: (1) as an acclimation period in which the participants become familiar with the act of tracking daily sodium intake and (2) for use as a baseline assessment from which an average daily sodium intake measure is calculated and the first daily sodium goal is issued. After this baseline monitoring period, users are asked to log their intake of high-sodium foods for a 3-day period approximately 2 weeks later. If the user meets their sodium goal (defined as submitting log data for all 3 logging days where all 3 values are less than or equal to the goal), then the user will be issued a new, lower goal based on the submitted data and will be asked to again intensively monitor their food intake 4 weeks later. Failure to meet the sodium goal during the logging period will prompt the system to ask the user to complete another 3-day logging period 2 weeks later. The sodium goals are calculated using the following algorithm:

For those who log an average of 2 to 6 items per day during their logging period, their new goal is 1 item less than the average.For those who log an average of 7 to 12 items per day during their logging period, their new goal is 2 items less than the average.For those who log an average of 13+ items per day during their logging period, their new goal is 3 items less than the average.

